## 2 Background

Surgery is the primary modality for the treatment of resectable gastric cancer, and radiotherapy can improve local control rates, but does the benefit of local control with postoperative radiotherapy translate into a survival benefit? The landmark INT-0116 study demonstrated that postoperative adjuvant radiotherapy (45 Gy/25 doses) given after radical surgery for gastric cancer increased 3-year survival from 41% to 50% ( $P < 0.001$ ), and the NCCN guidelines recommend postoperative adjuvant radiotherapy for patients with postoperative stage T2N0M0 and above. However, the lack of standardisation of the surgical approach and the fact that D2 resection accounted for only 10% of the patients in this study have led to ongoing controversy. To address this issue, the Korean ARTIST phase III study focused on postoperative D2 patients and showed that concurrent radiotherapy (45 Gy/25 sessions) improved DFS by 5.2% in the lymph node-positive subgroup, although it did not improve overall DFS ( $P=0.0365$ ). This result suggests the need to re-evaluate the precise benefit of radiotherapy in the post-D2 population.

Moreover, our department has previously conducted a phase I/II clinical study of the FOLFOX regimen combined with synchronous radiotherapy (at a dose of 50.4 Gy) after gastric cancer surgery, which confirmed the efficacy and safety of 50.4 Gy of radiotherapy combined with synchronous chemotherapy. The results of the phase II clinical study showed that the 1- and 2-year OS and DFS of the FOLFOX regimen combined with synchronous after radical D2 surgery were 95%, 82% and 85%, 78%. And the phase I/II clinical study of SOX regimen combined with synchronous radiotherapy after gastric cancer has been completed, after which the maximum tolerated dose (maximum tolerated dose, MTD) and safety of S-1 during synchronous radiotherapy have been explored. On this basis, I expect to further develop this multicenter phase III randomized controlled clinical study to explore the value of SOX regimen combined with simultaneous radiotherapy in the adjuvant treatment of gastric cancer patients after D2 radical surgery.

## 3 Objectives

The patients after D2 radical surgery for gastric cancer that meet the enrolment criteria were randomly assigned to be given SOX regimen combined with simultaneous radiotherapy or chemotherapy with SOX regimen alone, to explore the value of simultaneous radiotherapy after D2 radical surgery for gastric cancer.

- (1) The primary objective was: disease free survival (DFS).
- (2) The secondary objectives were: overall survival (OS), and various types of adverse events.

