| Title                  | Adjuvant chemoradiotherapy compared with adjuvant chemotherapy for gastric cancer after D2 gastrectomy: a multicenter phase III randomised controlled trial                                                                                                                                                                                                                                                                                                                                                                                                                                                                                                                                                                                                                                                                                                                                                                                                                                                                                                                                                                                                                                                                                                                                                                                                                                                                          |

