| Randomization        | Patients were assigned in a 1:1 ratio to SOXRT arm or SOX arm by block randomization.                                                                                                                                                                                                                                                                                                                                                                                                                                                                                                                                                                                   |
| Treatment            | 
This is a multicenter, phase III clinical trial led by West China Hospital, Sichuan University. Patients will be randomly assigned to either the SOXRT arm (experimental group) or the SOX arm (control group).
 
SOXRT arm: Patients will receive one cycle of induction chemotherapy with the SOX regimen 21 days prior to radiotherapy initiation, followed by S-1-based concurrent chemoradiotherapy. After completing radiotherapy, patients will undergo three additional cycles of SOX chemotherapy, with the same dosing regimen as in the induction chemotherapy.
 
SOX arm: Patients will receive a total of six cycles of SOX chemotherapy.
 |
| Statistical Analysis | 
Categorical variables were compared with the use of Chi-squared test or Fisher' s exact test. Kaplan – Meier method was used to analyses the DFS and OS, log-rank test to assess the significance, and Cox proportional hazards model to calculate hazard ratio (HR). The median follow-up time was calculated by reverse-KM method. Statistical significance was defined as a two-side P value < 0.05.
                                                                                                                                                                                                                                                       |

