## 4 Trial design

4.1 Randomisation: patients who met the inclusion criteria and signed the informed consent

were randomly grouped into a synchronous radiotherapy group (experimental group) and a chemotherapy-only group (control group) in a 1:1 ratio.

4.2 The protocol of the experimental group: one cycle of induction chemotherapy (SOX) was administered 21 days before radiotherapy; the specific dosage of SOX was S-1 30-40mg/m^2 bid D1-14, oxaliplatin 130mg/m^2 D1,Q3W, and then S-1 simultaneous radiotherapy was started, and the dosage of S-1 was 50mg bid during the period of simultaneous radiotherapy, which was used in combination with radiotherapy for 5 days a week for a consecutive period. in combination, 5 days per week for 28 days. After 3-4 weeks of radiotherapy, the SOX regimen was administered for 3 cycles at the same dose as the induction chemotherapy.

4.3 Control regimen: A total of 6 cycles of SOX regimen (at the same dose as in the experimental group) will be given.

4.4 Radiotherapy: radiotherapy was started within 3 months after surgery. The radiotherapy dose was 50.4 Gy/28f, 1.8 Gy/d, 5f/w. Radiotherapy was given on the 1st-5th day of each week for 28 consecutive days; radiotherapy was given by three-dimensional conformal radiotherapy (3D-CRT) or intensity-modulated radiotherapy (IMRT).

i. Radiotherapy localisation: fasting for 4 hours before localisation; supine position, hands on elbows, body mould fixation, CT simulation localisation, enhanced scanning, scanning range from T6 lower edge to L4 lower edge, layer thickness 3mm.

ii. Radiotherapy target zone (CTV) reference: postoperative radiotherapy target zone of gastric cancer includes tumour bed, anastomosis and regional lymph nodes. For the specific outlining method of target area, refer to 'Annex 1 Specification for Outlining Target Area of Postoperative Radiotherapy for Gastric Cancer' provided in this protocol.

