# 10 Study assessment

10.1 Effective evaluation indicators: The primary purpose is: DFS. The secondary purpose is: and OS.

10.2 Safety evaluation index: including all toxic side effects and adverse events observed during the trial.

10.3 Sample content estimation: we hypothesised that synchronous radiotherapy would result in higher DFS. with a double significance level of 0.05 and a certainty of 80%. We expect that the 3-year DFS of SOX regimen combined with simultaneous radiotherapy can be at least 8% higher than that of the chemotherapy-only group, i.e., from 70% to 78%. Based on the sample size formula for the comparison of the two sample rates, the sample size needed for this project was calculated to be 516 patients; assuming that 20% of the patients would need to be excluded from the statistics, the total number of patients that would need to be enrolled in this project would be 620.

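### Section 3 and the 10.3 hypothesis name radiotherapy as what is tested, but the arms also differ by two SOX cycles: a null result, an effect size, or equal or lower toxicity is not the effect of radiotherapy alone

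*Protocol*

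**What the plan says.** Two places in the Protocol make radiotherapy the thing under test. Section 3 (Objectives) says the randomised comparison is meant "to explore the value of simultaneous radiotherapy after D2 radical surgery for gastric cancer". Section 10.3, where the sample size is set, opens with "we hypothesised that synchronous radiotherapy would result in higher DFS".

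Other places describe a comparison of whole treatments. The title reads "Adjuvant chemoradiotherapy compared with adjuvant chemotherapy for gastric cancer after D2 gastrectomy". The closing aim of section 2 (Background) is "to explore the value of SOX regimen combined with simultaneous radiotherapy in the adjuvant treatment of gastric cancer patients after D2 radical surgery". Section 8.2 is worded in much the same way, and the second half of 10.3 contrasts 3-year DFS between the combined-treatment arm and the chemotherapy-only arm.

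The arms are stated consistently:

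- **SOXRT, section 4.2:** "one cycle of induction chemotherapy (SOX) was administered 21 days before radiotherapy", then S-1 with radiotherapy, and afterwards "the SOX regimen was administered for 3 cycles at the same dose as the induction chemotherapy". The synopsis agrees: "patients will undergo three additional cycles of SOX chemotherapy".
- **Control, section 4.3:** "A total of 6 cycles of SOX regimen (at the same dose as in the experimental group) will be given".

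The Protocol does not comment on the difference in the number of SOX cycles, and no third arm isolates radiotherapy.

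**The concern.** Section 3 reads as an add-on question: what does radiotherapy contribute on top of SOX? That calls for arms that share the same chemotherapy. Here the experimental arm gains radiotherapy with S-1 and gives up two oxaliplatin-containing cycles, so the randomised contrast is the net of the two changes.

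What is at stake is the conclusion, not the validity of the comparison. Read against section 3, a hazard ratio near 1 would answer that radiotherapy has no value after D2 surgery. The same result would also arise if radiotherapy helped and the omitted SOX cycles took the gain away. Adverse events are a secondary objective, and similar or lower systemic toxicity in SOXRT could reflect the smaller amount of oxaliplatin rather than good tolerance of radiotherapy.

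**Working it through.** The Protocol gives no cumulative doses, so there is no stated figure to reproduce. The sample-size totals of 516 and 620 play no part in this point.

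**Inputs from section 4.** Each SOX cycle has oxaliplatin 130 mg/m2 on day 1 and S-1 30-40 mg/m2 twice daily on days 1-14. During radiotherapy, S-1 is 50 mg twice daily and no oxaliplatin is listed. Radiotherapy is 28 fractions, 5 per week.

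**Assumed, not in the Protocol.** Body surface 1.5-1.8 m2.

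**SOX cycles.** SOXRT 1 + 3 = 4; control 6.

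**Planned oxaliplatin.** SOXRT 4 x 130 = 520 mg/m2; control 6 x 130 = 780 mg/m2. The ratio is 520/780 = 0.667, or 33% less.

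**Planned S-1.** Control = 6 x 14 x 2 x dose. SOXRT = 4 x 14 x 2 x dose + (treatment days x 100 mg)/body surface. With 28 treatment days (2800 mg):

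| S-1 dose | Body surface | SOXRT (mg/m2) | Control (mg/m2) | Ratio |
|---|---|---|---|---|
| 30 mg/m2 | 1.5 m2 | 3360 + 1867 = 5227 | 5040 | 1.04 |
| 30 mg/m2 | 1.8 m2 | 3360 + 1556 = 4916 | 5040 | 0.98 |
| 40 mg/m2 | 1.5 m2 | 4480 + 1867 = 6347 | 6720 | 0.94 |
| 40 mg/m2 | 1.8 m2 | 4480 + 1556 = 6036 | 6720 | 0.90 |

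Sections 4.2 and 4.4 give both a five-day week and a 28-day period, and the two need reconciling. If the period meant 28 calendar days with S-1 on five days a week, there would be 20 S-1 days (2000 mg). The ratio would then run from (4480 + 1111)/6720 = 0.83 to (3360 + 1333)/5040 = 0.93. On either reading, the larger imbalance is in oxaliplatin.

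**What dilution could look like.** Take the planned change in 3-year DFS from 70% to 78% as the effect of radiotherapy alone. Under proportional hazards, HR = ln(0.78)/ln(0.70) = 0.697. Suppose losing two SOX cycles multiplies the hazard by g. The Protocol gives no value for g, so those below are illustrative. Observed HR = 0.697 x g, and SOXRT 3-year DFS = 0.70^HR.

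| g | Observed HR | SOXRT 3-year DFS | Gain over 70% |
|---|---|---|---|
| 1.00 | 0.697 | 78.0% | 8.0 points |
| 1.05 | 0.731 | 77.0% | 7.0 points |
| 1.10 | 0.766 | 76.1% | 6.1 points |
| 1.20 | 0.836 | 74.2% | 4.2 points |

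Complete cancellation would need g = 1/0.697 = 1.44. A modest loss therefore does not erase the planned effect, but it shrinks it and makes a non-significant result more likely.

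**Direction.** If g is at least 1, the observed HR is never more favourable to SOXRT than the HR for the chemoradiotherapy component. The ambiguity therefore runs one way for efficacy.

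**The case against.** The strongest reply is that this is a disclosed design choice. Both regimens are written out, the synopsis and section 4 agree, and section 3 does not promise equal cycle numbers. The title, the closing aim of the background, section 8.2 and the second half of 10.3 already describe a comparison of strategies, and randomisation makes that comparison valid. Planned S-1 is roughly preserved. Planned duration is also similar: 3 + 5.6 + 3 to 4 + 9 = 20.6-21.6 weeks in SOXRT (28 fractions at 5 per week) against 6 x 3 = 18 in control. Radiotherapy-related toxicity has its own RTOG assessment in section 9.2. Exposure tables usually belong in a statistical analysis plan.

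Most of this stands, and it narrows the point. It does not remove it, because the formal objective and the opening hypothesis are fixed in this document and carry the question that the design does not isolate. Section 2 itself also asks whether the local control gained from radiotherapy turns into survival.

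A reader might infer that no DFS, OS or toxicity result could be attributed to radiotherapy. The documents do not support that. Unless less oxaliplatin improves outcome, an advantage for SOXRT cannot come from the omitted cycles, so a positive result still supports the chemoradiotherapy component and, if anything, understates it. An excess of toxicity in SOXRT despite less oxaliplatin would likewise point to that component. Nor does the Protocol say how a null result will be reported. The risk lies in what section 3 would permit.

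**Conclusion.** The point holds as a mismatch between the stated objective and the contrast that is randomised. The arms differ by S-1 chemoradiotherapy and by two of six SOX cycles, with planned oxaliplatin 33% lower in SOXRT. Three readings are not available as effects of radiotherapy alone: a null or negative DFS or OS result, the size of any effect, and equal or lower systemic toxicity in SOXRT. A positive DFS result or excess SOXRT toxicity remains interpretable in favour of the chemoradiotherapy component.

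The cycle and oxaliplatin figures follow directly from section 4. The rough match in S-1 rests on the assumed body surface and on 28 treatment days. The one-way argument rests on the assumption that less oxaliplatin does not itself improve outcome. The dilution table is illustrative, since the Protocol gives no effect for two SOX cycles. The correction should be made: it changes what the trial may conclude, though not its test or its size.

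**What to change.** Leave both regimens as they are, and change the wording as follows.

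1. Restate section 3 and the opening hypothesis of 10.3 as a comparison of two adjuvant strategies: SOX (4 cycles) plus S-1 chemoradiotherapy against SOX (6 cycles). This matches the title, the closing aim of section 2 and section 8.2, which needs no change.
2. State that a null DFS or OS result will not be concluded as radiotherapy having no value. No matching disclaimer is needed for a positive result.
3. State that the adverse event comparison will be interpreted alongside oxaliplatin and S-1 exposure by arm.

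The cost is a wording amendment and one exposure summary. The Protocol does not say that cumulative dose or completed cycles are recorded, although the dose-reduction rules in 5.3 presuppose that doses are tracked, so the sponsor should confirm that these data are captured. The downside is a narrower claim than the value of radiotherapy itself.

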## 4 Trial design

4.1 Randomisation: patients who met the inclusion criteria and signed the informed consent

were randomly grouped into a synchronous radiotherapy group (experimental group) and a chemotherapy-only group (control group) in a 1:1 ratio.

4.2 The protocol of the experimental group: one cycle of induction chemotherapy (SOX) was administered 21 days before radiotherapy; the specific dosage of SOX was S-1 30-40mg/m^2 bid D1-14, oxaliplatin 130mg/m^2 D1,Q3W, and then S-1 simultaneous radiotherapy was started, and the dosage of S-1 was 50mg bid during the period of simultaneous radiotherapy, which was used in combination with radiotherapy for 5 days a week for a consecutive period. in combination, 5 days per week for 28 days. After 3-4 weeks of radiotherapy, the SOX regimen was administered for 3 cycles at the same dose as the induction chemotherapy.

4.3 Control regimen: A total of 6 cycles of SOX regimen (at the same dose as in the experimental group) will be given.

4.4 Radiotherapy: radiotherapy was started within 3 months after surgery. The radiotherapy dose was 50.4 Gy/28f, 1.8 Gy/d, 5f/w. Radiotherapy was given on the 1st-5th day of each week for 28 consecutive days; radiotherapy was given by three-dimensional conformal radiotherapy (3D-CRT) or intensity-modulated radiotherapy (IMRT).

i. Radiotherapy localisation: fasting for 4 hours before localisation; supine position, hands on elbows, body mould fixation, CT simulation localisation, enhanced scanning, scanning range from T6 lower edge to L4 lower edge, layer thickness 3mm.

ii. Radiotherapy target zone (CTV) reference: postoperative radiotherapy target zone of gastric cancer includes tumour bed, anastomosis and regional lymph nodes. For the specific outlining method of target area, refer to 'Annex 1 Specification for Outlining Target Area of Postoperative Radiotherapy for Gastric Cancer' provided in this protocol.

iii. Radiotherapy plan: 3D-CRT or IMRT technology is used; PTV is externally applied in the anterior-posterior and left-right directions by 0.8 cm on the basis of CTV, and externally applied in the up-and-down direction by 1.0 cm; 95% of the PTV has a minimum dose of 50.4 Gy/28f; hotspot dose is  $\leq 107\%$  of the prescribed dose, and the volume is  $\leq 2$  CC; the target area conformity is  $\geq 0.8$ ; spinal cord is  $\leq 40$  Gy, and the liver V30 is  $\leq 33\%$  of the dose. The maximum dose received by 33% of the volume of one kidney (mostly right kidney) is  $<15$  Gy, and the average of both kidneys is  $<15$  Gy; D50 of small intestine is  $<20-30$  Gy.

4.5 Effectiveness evaluation: patients should undergo effectiveness evaluation at least once every 6 months during the first year after enrolment; after the end of treatment, regular follow-up and effectiveness evaluation should be conducted in accordance with the requirements of the supervising physician, and effectiveness evaluation should be conducted

at least once every 6-12 months. The time intervals of the evaluation should all be referenced to the point in time when the patient was randomised to the group. The evaluation includes physical examination, imaging (CT, chest radiograph, ultrasound, etc.) and laboratory tests (routine blood, blood biochemistry, tumour markers, etc.). The primary study endpoint was 3-year DFS, which was defined as the time from randomisation to the occurrence of tumour recurrence/metastasis (i.e., disease progression), or death in the randomised group; the secondary study endpoint of 3-year OS referred to the time from randomisation to death; and safety was also included.

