## **5 Selection of Patients**

### **5.1 Inclusion Criteria**

- (1) Age 18-70 years;
- (2) Gastric cancer patients who have been diagnosed by pathology and have been surgically resected;
- (3) Surgery is radical, achieving R0 resection, and D2 lymph node dissection (with organ preservation) (the number of lymph node dissection should be  $\geq 15$ );
- (4) The time to surgery is not more than 3 months;
- (5) According to the 2010 edition of UICC/AJCC staging criteria, postoperative pathological stage T stage  $\geq$  T4a, N stage  $\geq$  N0; and no tumour metastasis or postoperative recurrence is detected by comprehensive examination, i.e., the M stage is M0;
- (6) ECOG PS score: 0-1;
- (7) Patients who have not received radiotherapy and systemic chemotherapy before or after surgery;
- (8) Normal function of major organs, i.e., the following indications are met:
  - i. routine blood tests need to meet the following criteria: HB  $\geq$  9g/dL, WBC  $\geq$  3.5/4.0 $\times$  10^9/L, PLT  $\geq$  100 $\times$  10^9/L
  - ii. Biochemical tests must meet the following criteria: Crea and BIL  $\leq$  1.0 times the upper limit of normal (ULN), ALT and AST  $\leq$  2.5 times the upper limit of normal (ULN).
- (9) Women of childbearing potential must have had a negative pregnancy test (serum or urine) 7 days prior to enrolment and be willing to use an appropriate method of contraception for the duration of the trial and for 8 weeks after the last dose. For males, surgical sterilisation should be applied or agreement to use an appropriate method of contraception for the duration of the trial or 8 weeks after the final dose.
- (10) Subjects voluntarily enrolled in the study, signed an informed consent form, were compliant, and cooperated with follow-up.

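### The entry limit and the radiotherapy start limit are both 3 months after surgery, yet 21 days of induction must fit between them, so late entrants assigned to SOXRT cannot follow their schedule

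*Protocol*

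**What the plan says.** Four statements in the protocol bear on the timing.

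- **Entry.** Section 5.1, criterion 4, repeated in the synopsis: "The time to surgery is not more than 3 months". Criterion 2 describes the population as "Gastric cancer patients who have been diagnosed by pathology and have been surgically resected", so the limit can only mean time elapsed since the operation.
- **No earlier chemotherapy.** Section 5.1, criterion 7: "Patients who have not received radiotherapy and systemic chemotherapy before or after surgery". Section 4.1 randomises "patients who met the inclusion criteria and signed the informed consent". The induction cycle therefore cannot be given before enrolment.
- **Induction in the experimental arm.** Section 4.2: "one cycle of induction chemotherapy (SOX) was administered 21 days before radiotherapy". The treatment row of the synopsis agrees: "one cycle of induction chemotherapy with the SOX regimen 21 days prior to radiotherapy initiation".
- **Radiotherapy start.** Section 4.4: "radiotherapy was started within 3 months after surgery".

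Section 4.3 gives the control arm six SOX cycles and states no start limit counted from surgery. No section gives an exception, a shorter entry window, or another date from which the radiotherapy limit would run.

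**The concern.** The entry limit and the radiotherapy limit have the same length and the same starting point, the operation. At least 21 days of protocol treatment must fit between them in the SOXRT arm. A patient who enters near the end of the permitted window is eligible. If assigned to SOX, that patient can comply. If assigned to SOXRT, the patient cannot satisfy both section 4.2 and section 4.4.

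The protocol thus creates deviations that no site can avoid, in one arm only, and does not say which rule yields. Different centres may resolve the conflict differently, which makes the delivered experimental treatment less uniform than the protocol describes. The deviations also depend on time since surgery. How they are later handled therefore matters for the randomised comparison.

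**Working it through.** **Inputs from the protocol.** Entry limit W = 3 months from surgery (5.1, criterion 4). Radiotherapy limit = the same W (4.4). Interval from the induction cycle to radiotherapy = 21 days (4.2 and synopsis), counted from the start of the cycle, which is the reading that leaves the smallest gap. Allocation 1:1 (4.1).

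**Assumptions.** W = 91 days, with 84 to 92 as the range. L, the lag from enrolment to the first induction dose, is not given; 0 is the most favourable case, and 7 and 14 days are shown for comparison.

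**Step 1: latest compatible entry day = W − 21 − L.**

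- W = 91, L = 0: 91 − 21 = day 70.
- W = 84, L = 0: day 63. W = 92, L = 0: day 71.
- W = 91, L = 7: day 63. W = 91, L = 14: day 56.

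**Step 2: earliest radiotherapy for a patient entering on day E = E + L + 21.** With E = 91 and L = 0, this is day 112, which is 21 days past the limit.

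**Step 3: part of the entry window that is incompatible with SOXRT = (21 + L)/W.**

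- W = 91, L = 0: 21/91 = 23% (21/92 = 23% to 21/84 = 25%).
- W = 91, L = 7: 28/91 = 31%. W = 91, L = 14: 35/91 = 38%.

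These are shares of calendar time, not of patients.

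**Step 4: share of patients entering in the gap.** This needs a distribution of entry times, which the protocol does not give. With L = 0, a 13-week window, a cut-off at week 10, and entry beginning at week s (all assumed):

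| First entry (week s) | All in by week 10 | Linear decline to zero at week 13: (3/(13 − s))² | Uniform to week 13: 3/(13 − s) |
|---|---|---|---|
| 2 | 0% | 7% | 27% |
| 3 | 0% | 9% | 30% |
| 4 | 0% | 11% | 33% |
| 6 | 0% | 18% | 43% |

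**Step 5: share of randomised patients who would deviate.** Only SOXRT patients can breach the limit, so with 1:1 allocation the figures halve: 0% in the first case, about 4% to 9% with declining entry, and about 14% to 21% with uniform entry.

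**The case against.** It can fairly be said that criterion 4 is loosely worded and does not say whether the 3 months end at consent, randomisation or first treatment. This does not remove the conflict. Even if the limit runs to first treatment, a first dose on day 91 puts radiotherapy at day 112.

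It can also be said that a radiotherapy limit can only apply to the arm that receives radiotherapy, and that criterion 4 applies to both arms equally before randomisation. That is true. The asymmetry is a consequence of the design; what is wrong is that the two limits are not coordinated.

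Two stronger inferences are tempting, and the protocol supports neither.

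- **That 27% to 43% of patients will violate the protocol.** Those figures assume uniform entry right up to week 13 and count both arms. With other entry patterns the share can be much lower, down to zero, and SOX patients cannot deviate on this rule.
- **That the DFS comparison will be biased by one-sided exclusions or by sites skipping induction.** Section 5.3 does not list a late radiotherapy start among its grounds for stopping treatment or leaving the study. The 20% in section 10.3 is a sample-size allowance without stated reasons, and nothing links it to late starters. Sections 6 and 11.1 require treatment strictly according to the plan, and nothing suggests that induction may be omitted. Section 4.5 counts DFS and OS from randomisation, so a patient whose radiotherapy starts late can still be followed and analysed in the assigned arm.

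What stands after these objections is the timing contradiction itself. No section resolves it, and an analysis plan cannot make the treatment rules compatible.

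**Conclusion.** The protocol contradicts itself on timing. With 3 months taken as 91 days and no lag to treatment, a patient who enters after day 70 is eligible but cannot follow the SOXRT schedule. About 23% of the calendar window is affected, and more with any lag. The contradiction needs no assumption about entry patterns.

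The number of patients affected is unknown. The illustrations run from 0% to 43% of entrants, with about half of those, the SOXRT patients, actually deviating.

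The direct consequence is built-in timing deviations in one arm. With no lag or other delay, the overshoot is at most 21 days. A reader might go further and conclude that the primary comparison is biased; that would require affected patients to be removed after randomisation, a step the protocol does not state. The point should be fixed, but on the evidence in the document it does not invalidate the trial.

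**What to change.** Reconcile inclusion criterion 4 (section 5.1 and synopsis), the induction timing (section 4.2 and synopsis) and the radiotherapy start limit (section 4.4), so that every patient eligible at randomisation can follow whichever schedule is assigned. Which of these limits changes is a clinical decision for the sponsor, and none is proposed here.

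Two conditions protect the comparison whichever limit changes. Any resulting entry limit should apply to both arms and be checked before randomisation. Patients whose radiotherapy nevertheless starts late should stay in their assigned arm. Criterion 4 should also name the date at which time since surgery is measured.

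The cost is an amendment of one eligibility or timing sentence, with the matching synopsis text. Any effect on recruitment depends on which limit the sponsor changes.

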### **III. Radiotherapy Planning**

1. 3D-CRT, IMRT should be used;
2. Based on the CTV, the PTV should be expanded by 0.8 cm in the anterior, posterior, left, and right directions, and by 1.0 cm in the cranial-caudal direction;
3. Minimum dose covering 95% of the PTV: 50.4 Gy in 28 fractions; hotspot dose  $\leq$  107% of the prescription dose, with hotspot volume  $\leq$  2 cc;
4. Conformity index (CI)  $\geq$  0.8;
5. Dose constraints for major organs at risk: spinal cord  $\leq$  40 Gy, liver V30  $\leq$  33%, the dose to 33% of the volume of one kidney (most commonly the right kidney)  $<$ 15 Gy, mean dose to both kidneys  $<$ 15 Gy; small bowel D50  $<$ 20-30 Gy.

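### The experimental-arm schedule in Protocol 4.2 and 4.4 contradicts itself on the length of radiotherapy, leaves the number of concurrent S-1 days open, and disagrees with the synopsis on when SOX resumes

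*Protocol*

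**What the plan says.** Three elements of the experimental arm are affected.

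**Radiotherapy.** Section 4.4 gives the prescription as "The radiotherapy dose was 50.4 Gy/28f, 1.8 Gy/d, 5f/w". The next sentence gives the timing: "Radiotherapy was given on the 1st-5th day of each week for 28 consecutive days". The planning requirement in 4.4 item iii repeats the dose ("95% of the PTV has a minimum dose of 50.4 Gy/28f"), and so does Appendix 2, part III ("Minimum dose covering 95% of the PTV: 50.4 Gy in 28 fractions").

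**Concurrent S-1.** Section 4.2 sets 50 mg twice daily during radiotherapy. The sentence on duration is broken and ends "in combination, 5 days per week for 28 days".

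**Later SOX cycles.** Section 4.2 says "After 3-4 weeks of radiotherapy, the SOX regimen was administered for 3 cycles at the same dose as the induction chemotherapy". The Treatment row of the synopsis says "After completing radiotherapy, patients will undergo three additional cycles of SOX chemotherapy" and gives no interval.

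**The concern.** These sentences define the experimental regimen, which is what the trial compares with SOX alone. Section 11.1 requires investigators to treat strictly according to the plan, but the sentences cannot all be obeyed together. Two careful sites could therefore arrive at different S-1 exposure or different spacing between radiation and oxaliplatin, and each could point to a sentence in support.

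The ambiguity also reaches trial conduct. Compliance and protocol deviations need one reference schedule. Two safety provisions depend on when radiotherapy ends: the rule in 5.3.3 for grade 4 toxicity during concurrent radiotherapy, and the acute radiation toxicity window in 9.2, which closes 28 days after radiation.

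**Working it through.** **Inputs.** 28 fractions, 1.8 Gy per day, five fractions per week, treatment on days 1 to 5 of each week, 28 consecutive days (all Section 4.4). S-1 50 mg twice daily, five days per week for 28 days, and SOX after three to four weeks of radiotherapy (Section 4.2).

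**1. The stated dose.** Fractions × dose per fraction = 28 × 1.8 Gy = 50.4 Gy. The plan's figure is reproduced, and it agrees with 4.4 item iii and Appendix 2.

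**2. Time needed for that dose.** 28 fractions ÷ 5 per week = 5.6 weeks. In calendar days, 25 fractions fill five full weeks (35 days) and three remain. A Monday, Tuesday or Wednesday start needs 35 + 3 = 38 days. A Thursday or Friday start runs into one more weekend and needs 40.

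**3. What 28 consecutive calendar days hold.** 28 ÷ 7 × 5 = 20 treatment days, whatever the start day. 20 × 1.8 Gy = 36.0 Gy, which is 8 fractions or 14.4 Gy below the prescription (36.0 ÷ 50.4 = 71.4%).

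**4. The three conditions together.** With 28 counted as calendar days, any two exclude the third:
- five per week for 28 consecutive days gives 20 fractions, not 28;
- 28 fractions at five per week take 38 to 40 days, not 28;
- 28 fractions in 28 consecutive days means seven per week, not five.

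If 28 counts treatment days, the fraction count and the weekly rate agree, but the days cannot be consecutive because each week has a two-day gap.

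**5. Concurrent S-1.** At 50 mg × 2 = 100 mg per day:
- 28 as calendar days: 20 dosing days, 20 × 100 = 2,000 mg;
- 28 as dosing days: 28 × 100 = 2,800 mg.

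The ratio is 2,800 ÷ 2,000 = 1.40, so the second reading gives 40% more (full dosing assumed, no reductions). No other section states the number of days.

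**6. Start of the later SOX cycles.** Read literally, at five fractions per week:
- 3 weeks = 15 fractions = 27.0 Gy, with 13 fractions still to give;
- 4 weeks = 20 fractions = 36.0 Gy, with 8 still to give.

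Both points fall inside a 5.6-week course, so SOX would overlap radiation, contrary to the synopsis. Read instead as an interval after radiotherapy ends, and with a Monday start, SOX would resume 38 + 21 = 59 to 38 + 28 = 66 days after radiotherapy begins, against 21 to 28 days on the literal reading. The two readings differ by the length of the whole course.

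**The case against.** The best defence is that the dose is never in dispute. It appears as 50.4 Gy in 28 fractions in 4.4, in the planning requirement and in Appendix 2, and a site that stopped early would breach that requirement. The number 28 matches the fraction count in the sentence before, and treatment limited to days 1 to 5 of each week cannot be literally consecutive, so the sentence itself strains against the calendar-day reading. The neighbouring text in 4.2 is visibly broken, which suggests a translation or transcription fault. The SOX phrase may likewise be a slip for an interval after radiotherapy, which would fit the synopsis.

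Much of this stands. A reader might infer from step 3 that the protocol prescribes, or that sites delivered, 36 Gy. The documents do not support that. No section states 20 fractions or 36 Gy, and the figure only measures how far one duration phrase departs from the prescription when taken literally. Nor does anything show that centres actually diverged, or that the trial could not say what radiation dose it tested.

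The defence does not remove the rest. It works for radiotherapy only by disregarding a word in 4.4. The repeated dose does not fix the number of S-1 days, and the synopsis does not supply the interval before SOX resumes.

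**Conclusion.** The concern holds as a contradiction in the schedule wording, not as a second radiation dose. Three items need correction:

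- the duration in 4.4: 28 consecutive days against 38 to 40 for the stated course;
- the concurrent S-1 days in 4.2: 20 or 28, a 40% difference in planned total;
- the SOX start in 4.2: literally after 15 to 20 of 28 fractions, against after completion in the synopsis.

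The first rests on the plain meaning of consecutive days. The second does not depend on which reading is intended, because either is open and no other text decides. The third is the weakest, since a slip of wording is plausible, but as written the two places disagree. The sample size and power calculation are not directly affected. Because these are operative treatment instructions with safety implications, and the correction is cheap, it should be made.

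**What to change.** Reconcile the 28-day wording in 4.2 and 4.4 with the 28-fraction, five-per-week prescription. State the number of concurrent S-1 dosing days once, in 4.2. Reconcile the start of the later SOX cycles in 4.2 with the synopsis, so that both use the same reference point and any interval is stated the same way. Appendix 2 deals with contouring and planning, already agrees on the dose, and needs no S-1 or SOX schedule. Which reading is intended is for the clinical team to decide; this review takes no position on it.

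The cost is a wording amendment, the ethics committee approval that Section 7 requires for any modification, and a notice to sites. No change to the sample size or the analysis follows.
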